#### 3.2.2. Secondary Outcome Variables

The secondary outcome variables will be 1. BMI. 2. Waist circumference. 3. Blood pressure. 4. Total cholesterol and LDL cholesterol. 5. Capillary blood glucose, and blood glucose, and HbA1c in the patients with diabetes. 6. Cardiovascular events, use of health services, emergency visits, and readmissions throughout of the study.

### 3.3. Statistical Analysis

The principles of intention-to-treat analysis will be followed. The differences between patients who gave up the app and those who were able to utilize it will also be examined by analyzing the outcome variables from the electronic medical record. A descriptive statistical analysis will be performed (mean, standard deviation, 95% confidence interval, frequencies, and percentages). For the comparison of means, the Student’s t-test will be used (normal distribution variables) and the Mann–Whitney U test (if the variables are non-normally distributed). The Chi-squared/Fisher test will be used for the comparison of proportions. The relative risks and 95% confidence intervals will be computed. The quantitative primary outcomes from the two groups will be compared using an analysis of covariance adjusted for age and gender. A sensitivity analysis will also be performed regarding the baseline characteristics of the participants in both groups and missing data. A multivariate analysis will be performed to examine the association of the intervention with lifestyle habits, control of the CVRFs and evolution after discharge regarding cardiovascular events, the use of health services, emergency visits, and readmissions using Kaplan–Meier survival analysis. A two-tailed *p*-value < 0.05 will be considered statistically significant. The SPSS v.24.0 software will be used. 24.0. The researchers analyzing the results will be blinded to the allocation of the participants.

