## Abstract

Coronary heart disease is one of the main causes of morbimortality around the world. Patients that survive a coronary event suffer a high risk of readmission, relapse and mortality, attributed to the sub-optimal control of cardiovascular risk factors (CVRF), which highlights the need to improve secondary prevention strategies aimed at improving their lifestyle and adherence to treatment. Through a randomized controlled clinical trial, this study aims to evaluate the effect of an intervention involving an online health application supported by a mobile telephone or tablet (mHealth) on lifestyle (diet, physical activity, and tobacco consumption) and treatment adherence among people with coronary heart disease after percutaneous coronary intervention. The sample will comprise 240 subjects (120 in each arm: intervention and usual care). They are assessed immediately and nine months after their hospital discharge about sociodemographic, clinical, CVRF, lifestyle, and treatment adherence characteristics. The educative intervention, involving a follow-up and self-monitoring, will be performed using an online mHealth tool consisting of an application for mobile phones and tablets. The quantitative primary outcomes from the two groups will be compared using an analysis of covariance (ANCOVA) adjusted for age and gender. A multivariate analysis will be performed to examine the association of the intervention with lifestyle habits, the control of CVRFs, and outcomes after discharge in terms of the use of health services, emergency visits, cardiovascular events and readmissions.

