## 3. Results

Thirty-six weeks after the initial assessment, all the patients are reassessed in terms of their lifestyle, risk factors, and treatment management. In the intervention group, the variables related to usability, and satisfaction with the application will also be appraised. The participant’s satisfaction with the treatment received will also be evaluated (using a questionnaire). Records will be taken of whether the patient has been referred to cardiac rehabilitation and their attendance. Records will also be kept of the cardiovascular events occurring during the study, the use of health services and emergency visits taken from electronic medical records.

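### The multivariate analysis of post-discharge outcomes names only Kaplan–Meier, which takes no covariates and counts only the first of any repeated visits

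*Protocol article*

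**What the plan says.** The sentence at issue is in section 3.3. It opens "A multivariate analysis will be performed to examine the association of the intervention with lifestyle habits, control of the CVRFs and evolution after discharge" and closes "evolution after discharge regarding cardiovascular events, the use of health services, emergency visits, and readmissions using Kaplan–Meier survival analysis". The article names no other method for this multivariate analysis. The Abstract announces the same analysis, "A multivariate analysis will be performed to examine the association of the intervention with lifestyle habits, the control of CVRFs, and outcomes after discharge", without naming a method.

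Section 3.2.2 places the outcomes concerned last among the secondary outcomes: "Cardiovascular events, use of health services, emergency visits, and readmissions throughout of the study". Section 3 says that service use and emergency visits come from electronic medical records.

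Elsewhere, section 3.3 names ANCOVA adjusted for age and gender for the quantitative primary outcomes, t or Mann–Whitney tests for means, chi-squared or Fisher tests for proportions, and relative risks with 95% confidence intervals. No regression model for event times or counts (Cox, logistic, Poisson, negative binomial or recurrent-event) appears anywhere in the article.

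**The concern.** There are two mismatches between the method and the task set for it.

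1. **Adjustment.** A multivariate association needs a model with covariates. Kaplan–Meier is a non-parametric curve for each group. With a log-rank test it gives an unadjusted comparison, or a stratified one at most.
2. **Recurrence.** One patient can have several emergency visits, service contacts or readmissions in 36 weeks. Time to first event ignores all but the first.

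Section 1 lists use of services, emergency visits and readmissions among the study's aims. If the sentence is followed literally, the adjusted association is never produced, and the comparison of service use may rest on part of the recorded data. If the analysts depart from it, their choice of model is open to challenge as made after the fact.

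**Working it through.** The plan states no figure for this analysis, so there is none to reproduce. The check has two parts.

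**Part 1: method against outcome**

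| Post-discharge outcome | Data | What Kaplan–Meier delivers | What it does not deliver |
|---|---|---|---|
| Cardiovascular events | Time to first event | Valid unadjusted curve | Adjusted effect |
| Readmissions | Time to first; can recur | Valid unadjusted curve for the first | Adjusted effect; later readmissions |
| Emergency visits, service contacts | Counts over follow-up | Curve for the first contact | Adjusted effect; all later contacts |

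No row gives the multivariate association that the sentence promises.

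**Part 2: how much is lost by keeping only the first visit**

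Inputs from the documents: 120 per arm (section 2.4), 36 weeks of follow-up (sections 2.6 and 3), two-sided 5% level (section 3.3).

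Inputs assumed, because the documents give none: mean visits per usual-care patient *m* = 0.2, 0.5, 1 or 2 over follow-up; rate ratio 0.7; gamma frailty variance θ = 0.5 to 1 for between-patient variation.

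*Share of visits ignored in usual care.* Patients with at least one visit contribute one each, so the share ignored is 1 − P(at least one visit)/*m*.

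- Poisson: 1 − (1 − e^(−m))/m. At *m* = 1 this is 1 − 0.632 = 37%.
- Gamma–Poisson with θ = 1: P(at least one) = m/(1 + m), so the share ignored is also m/(1 + m). At *m* = 1 this is 50%.

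*Power of a rate comparison on all visits.* The standard error of the log rate ratio is √{[(1/m + θ) + (1/(0.7m) + θ)]/120}, and |ln 0.7| = 0.357.

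- *m* = 1, θ = 0.5: √[(1.5 + 1.929)/120] = 0.169; z = 0.357/0.169 = 2.11; power ≈ Φ(2.11 − 1.96) = 56%.
- *m* = 0.2, θ = 1: √[(6 + 8.143)/120] = 0.343; z = 1.04; power ≈ Φ(1.04 − 1.96) = 18%.

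These agree with simulation to within a few points. Power of the log-rank test on the first visit was obtained by simulation under the same inputs.

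| Mean visits, usual care | Share ignored, Poisson | Share ignored, θ = 1 | First-visit log-rank power | All-visit rate model power |
|---|---|---|---|---|
| 0.2 | 9% | 17% | about 16% | about 17% |
| 0.5 | 21% | 33% | 25–29% | 31–36% |
| 1 to 2 | 37–57% | 50–67% | 30–48% | 46–77% |

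Power ranges are over θ = 0.5 to 1 and, in the last row, over both means. The loss is close to nil when events are rare and large when visits are common.

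**The case against.** The strongest reply has four parts.

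*The wording attaches Kaplan–Meier only to the last item of the list.* This is the natural reading, and the Abstract, which omits Kaplan–Meier, supports it. A reader might infer that the plan applies Kaplan–Meier to lifestyle habits and risk-factor control, which are reassessed once, at 36 weeks, and have no event time. The text does not require that. Habits that are quantitative primary outcomes have the adjusted ANCOVA, and a model not named for the rest may be left to a fuller document. The reply does not rescue the post-discharge outcomes, where Kaplan–Meier is named and is still unadjusted.

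*Other planned analyses fill part of the gap.* Relative risks with confidence intervals are planned, and Mann–Whitney could compare visit counts. A reader might infer that the plan offers no effect size for these outcomes, or that every visit after the first is certainly lost. Neither follows: relative risks could serve for the proportion with an event, Kaplan–Meier itself gives event-free proportions, and the article does not say that it is the only analysis of service use. Yet none of these methods is covariate-adjusted.

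*Adjustment is optional in a 1:1 randomised trial.* An unadjusted comparison of time to first event is valid, but the plan itself promises a multivariate one.

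*The time origin is not in conflict.* A reader might infer that counting from discharge clashes with randomisation in hospital. The article defines no time zero for the curves and does not fix the moment of randomisation, so no contradiction can be shown.

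The absence of an analysis plan is no defence here. The article does name a method, and that method cannot do what its own sentence says.

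**Conclusion.** The point holds for the post-discharge outcomes: the sole method named for their multivariate analysis cannot adjust, and for recurring outcomes it uses only first occurrences. The first part needs no assumption. The size of the second rests on assumed visit rates, frailty and effect. Under those inputs the power difference runs from about one percentage point at 0.2 visits per patient to roughly 30 points in the most favourable case at 2 visits. It may therefore be negligible for rare outcomes, possibly including cardiovascular events and readmissions, and substantial for frequent service contacts.

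This is a should-fix. A reader might rank it as essential, but the outcomes are secondary, the sample size in section 2.4 does not rest on them, and the quantitative primary outcomes have their own analysis.

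**What to change.** Replace the Kaplan–Meier clause in section 3.3, or settle it in the analysis plan, so that it states:

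- **Time to first cardiovascular event and first readmission:** Kaplan–Meier curves with a log-rank test as the unadjusted display, and Cox regression timed from randomisation and adjusted for age and gender (the covariates already named for the ANCOVA) for the adjusted effect.
- **Emergency visits and health-service contacts:** negative binomial regression, or Poisson with robust standard errors, with follow-up time as offset, so that all visits count.

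The cost is one revised sentence and a little more analysis. No new data are needed beyond the dates and counts in the electronic records. The article reports 95 of the planned 240 patients recruited, so at that stage the wording could still be settled before outcomes are analysed.

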## 4. Discussion

Maintaining lifestyle changes and healthy behavior is the key to achieving improved clinical outcomes in patients with cardiovascular diseases (CVD). Thus, ongoing contact with the patient is necessary. The strategies used in studies to achieve behavioral changes and healthier lifestyles include: individual guidance, informing the patients of risks, shared decision-making, participation of family members, setting goals for treatment adherence, the control of CVRFs, and motivating participants. Modern technology can help in implementing these strategies. To this end, there has been increasing interest recently in research into mHealth resources for the prevention of CVD [21,27]. However, there is a lack of evidence about their efficacy and about the features of applications that increase commitment and effectiveness.

The present project acts to improve both lifestyle and treatment adherence through a remote, personalized intervention using limited material and human resources aimed at improving the outcome of these patients. The intervention is designed to be integrated into the care given to cardiac patients from the moment of their admission and aims to consolidate the activities the usual care given to these patients. Additionally, secondary prevention begins during the hospital stay, a stage in which the patients and their families are very receptive to advice from medical staff as the coronary event is very recent.

This study, involving a CRT, will provide fresh evidence about the viability and efficacy of a mHealth application for improving adherence to treatment and lifestyle among patients with coronary heart disease. An application will be tested that has been designed by health professionals and IT engineers following international guidelines [31]. In addition to the data recorded by patients in the application, objective clinical measurements will be taken such as BMI, waist circumference, blood pressure (BP), carbon monoxide in exhaled air, as well as laboratory results such as cholesterol, lipoproteins, blood glucose, and HbA1c. An analysis will also be performed of the usability of the application and the patients’ satisfaction and commitment, as well as important features of the application that can enhance its efficacy and use.

### Limitations of the Study

To use this tool, it is necessary to have a mobile telephone and internet connection, conditions that are met by a growing number of people of the age of the target population in our country, evidence of which is the current statistics presented in the introduction. The recruitment will take place in a city hospital and differences may exist in rural areas. However, the hospital treats patients from different regions of the province, thus providing information about the reach of this intervention. The possible participants are volunteers and are likely, therefore, to be more motivated, although this is a more general limitation regarding less motivated people and not a selection bias since the study design is a randomized clinical trial.

## 5. Conclusions

The use of new technology and applications for smartphones is an appealing tool in secondary prevention strategies for CVD. Therefore, there is a need for more evidence about their usefulness for monitoring patients that will be of use to health professionals and medical services. The study will provide evidence about the effectiveness of an mHealth intervention that may be transferable and used to encourage adherence to recommendations about healthy lifestyles and treatment with pharmacological treatment in cardiovascular disease and other chronic illnesses.

## Figures and Tables

**Figure 1 nutrients-13-01818-f001:**
[figure not shown]
Flow Diagram. CVRF: cardiovascular Risk factors; PCI: percutaneous coronary intervention.

**Figure 2 nutrients-13-01818-f002:**
[figure not shown]
Start page app of the EVITE project.

**Figure 3 nutrients-13-01818-f003:**
[figure not shown]
Diet, physical activity, and treatment modules (from left to right).

**Figure 4 nutrients-13-01818-f004:**
[figure not shown]
Body weight, body mass index (BMI), blood pressure, capillary blood glucose and tobacco modules (from left to right). * Body weight and height to calculate BMI.

**Figure 5 nutrients-13-01818-f005:**
[figure not shown]
Weekly feedback traffic light and messages.

**Figure 6 nutrients-13-01818-f006:**
[figure not shown]
Record: graphics of evolution and progress of body mass index, blood pressure, body weight and waist circumference, and capillary blood glucose (from left to right).
